### Additional analyses {20b}

Pre-specified subgroup analyses will examine treatment effect heterogeneity across key demographic and clinical variables, including age subgroups (20–35 vs. 36–50 years), baseline depression severity (HAM-D-17 scores 20–25 vs. ≥ 26), and trauma history (present vs. absent). These analyses will be conducted using interaction terms within mixed-effects models, with Bonferroni correction applied for multiple comparisons (adjusted *α* = 0.0167). Exploratory analyses will assess dose–response relationships using marginal structural models incorporating session attendance and homework completion rates. Sensitivity analyses will evaluate the robustness of findings by comparing per-protocol and intention-to-treat populations and by examining missing data patterns using Little’s MCAR test. For the online intervention arm, platform engagement metrics (e.g., login frequency and session duration) will be examined in relation to outcomes using partial least squares regression. All subgroup analyses will be interpreted as hypothesis-generating due to limited power, with effect sizes reported alongside 95% confidence intervals rather than relying solely on *p*-values.

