### Clients selection and sample size {14}

The study focuses on individuals with MDD in Pakistan, specifically selecting geographically accessible participants residing in the major cities of Rawalpindi, Islamabad, and Peshawar. Recent literature cites various studies such as by Ishtiaq et al. [56], Noor et al. [57] and Umar et al. [58] on the high prevalence of depressive disorders in these three cities of Pakistan. However, since the exact number of MDD cases in these three major cities is unknown, a more customized, multi-stage sampling procedure has been adopted.

Initially, three rehabilitation centers located in the selected cities will be randomly but purposively picked for recruiting patients. The centers will not be chosen fully at random; rather, the characteristics of the vicinity and patient flow into centers will be considered. Within each selected center, clients will be recruited using a sequential consecutive sampling technique with a rolling enrollment strategy. This approach involves selecting every eligible patient who meets the inclusion criteria until the required sample size is achieved [59]. The estimated sample size of (*n* = 80) was calculated by using the below given approximation method for two independent group means, as recommended in the existing literature by Sakpal [60] and Chow [61]:$$n=\frac{\left({Z}_{\frac{\alpha }{2}}+{Z}_{\beta }{)}^{2}\cdot (2{\sigma }^{2}\right)}{\left({M}_{1}-{M}_{2}{)}^{2}\right.}$$where.

*n*= is the estimated sample size.

Zα/2 = is the Z-score matching to the desired α level (for e.g., 1.96 for 95% confidence).

Z*β* = is the Z-score matching the desired power level (for e.g., 0.84 for 80% power).

σ^2^ = is the pooled variance of two groups.

µ​_1_ - µ​_2_= are the expected difference in means of depression scores.

A two-sided significance level of α = 0.05 was selected, consistent with conventional recommendations for clinical trials, resulting in α/2 = 0.025 and a corresponding Z-score of 1.96. Statistical power was set at 80% (1 − β = 0.80), yielding β = 0.20 and a corresponding Z-score of 0.84.

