### Eligibility criteria {10}

Each consecutive client in the selected centers will undergo Structured Diagnostic Interview for Screening DSM-5 (TR) Disorders [63] for an initial MDD diagnosis. Additionally, patients will be assessed for eligibility based on the below given inclusion criteria:i.The clients should exhibit symptoms of MDD.ii.Male and female clients will be selected equally.iii.Clients between the ages of 20 and 50 will be selected. It was because this study is not on children or older clients.iv.Clients should preferably be "treatment-naive," meaning they have no recent history of any psychotherapy or medication. This ensures that the adapted EMDR therapy can be implemented effectively without interference from previous therapies and to avoid confounding effects.v.There must be no significant neuropsychological or cognitive disorders among patients.vi.MDD with comorbid Anxiety is permitted in this study; however, clients should not have any other comorbid symptoms.

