### Who will take informed consent? {26a}

Following initial screening interviews and administration of the Hamilton Depression Rating Scale-17 (score ≥ 20) and Generalized Anxiety Disorder Questionnaire-IV (score ≥ 5.7), eligible clients will undergo final eligibility assessment (see Eligibility Criteria). Therapists will notify all selected clients of their inclusion in the study. Clients will then receive the study information and consent materials. The therapists will obtain written informed consent from willing clients.

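### Age and baseline HAM-D-17 are tested as effect modifiers only in two-level form; continuous interaction terms would be more precise if modification is roughly linear

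*Protocol article*

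**What the plan says.** Additional analyses {20b} of the protocol article names three effect modifiers. Trauma history is binary by nature. The other two are given as two-level groups: "age subgroups (20–35 vs. 36–50 years), baseline depression severity (HAM-D-17 scores 20–25 vs. ≥ 26". On method the section says: "These analyses will be conducted using interaction terms within mixed-effects models", "with Bonferroni correction applied for multiple comparisons", with an adjusted alpha of 0.0167. It adds that "All subgroup analyses will be interpreted as hypothesis-generating due to limited power", and that effect sizes with 95% confidence intervals will be reported rather than p-values alone.

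Both grouped variables are numeric at source. Under Eligibility criteria {10}, "Clients between the ages of 20 and 50 will be selected". The consent section {26a} describes screening by "administration of the Hamilton Depression Rating Scale-17 (score ≥ 20", so baseline severity is a score from 20 upwards. The article nowhere plans to test either interaction with the variable left as a number.

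**The concern.** Cutting a numeric modifier in two makes clients aged 35 and 36 different in the model, and clients aged 20 and 35 alike. The same happens at 25 and 26 points. If the difference between online and in-person delivery changes gradually with age or severity, the two-level interaction term estimates that change less precisely than a continuous term fitted to the same data.

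The plan already concedes that power is limited here. The cut lowers it further, and it widens the confidence intervals on which the plan wants readers to rely. At stake is the precision of two exploratory results, not the trial's main conclusion.

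**Working it through.** **The plan's own figure.** Three modifiers at an overall 0.05: 0.05/3 = 0.0167. This reproduces. The two-sided critical value is z = 2.394.

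**Inputs from the document.** SD of change 8 points, and 80 clients for analysis in a 1:1 ratio (Clients selection and sample size {14}; Sequence generation {16a}); age 20 to 50, cut at 36; HAM-D-17 from 20, cut at 26.

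**Inputs assumed.** The distributions of age and baseline HAM-D-17, a modifier effect linear in the variable, and the size D of the interaction (the difference between the two subgroups in the arm effect). The document gives none of these.

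**Formulas.** Let p be the share at or above the cut, d the difference in mean x between the two groups, and SD(x) the standard deviation of the modifier.
- Information kept by the cut: r² = d² p(1 − p)/SD(x)²
- SE of the two-level interaction: (2 × 8/√80)/√(p(1 − p)) = 1.789/√(p(1 − p))
- SE of the interaction slope: 1.789/SD(x), with true slope D/d
- Power: Φ(effect/SE − 2.394)

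**Worked case: age uniform over the integers 20 to 50.** p = 15/31 = 0.484; d = 43 − 27.5 = 15.5; SD(x) = 8.944.
- r² = 240.25 × 0.2497/80 = 0.75, so 25% of the information is lost.
- Two-level, D = 5: SE = 3.58; 5/3.58 = 1.397; power = Φ(−0.997) = 16%.
- Continuous, D = 5: slope 5/15.5 = 0.3226; SE = 0.200; ratio 1.613; power = Φ(−0.781) = 22%.

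**Other near-central cases.** The HAM-D-17 rows are rounded normals truncated at 20, and the second age row is a normal restricted to 20–50. Both are labelled by mean and SD before truncation. The power columns show two-level → continuous.

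| Modifier, assumed distribution | p | r² | D = 3 | D = 5 | D = 10 |
|---|---|---|---|---|---|
| Age, uniform | 0.48 | 0.75 | 6% → 8% | 16% → 22% | 66% → 80% |
| Age, normal (35, 8) | 0.47 | 0.68 | 6% → 8% | 16% → 24% | 65% → 84% |
| HAM-D-17 (24, 4) | 0.41 | 0.68 | 6% → 8% | 15% → 23% | 64% → 83% |
| HAM-D-17 (22, 5) | 0.35 | 0.68 | 6% → 8% | 14% → 22% | 61% → 80% |
| HAM-D-17 (26, 4) | 0.58 | 0.64 | 6% → 9% | 16% → 25% | 64% → 86% |
| HAM-D-17 (20, 6) | 0.34 | 0.68 | 6% → 8% | 14% → 21% | 60% → 79% |

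Across these rows, 80 clients analysed with the cut are worth about 51 to 60 analysed without it (80 × 0.64 to 80 × 0.75). A wider set of near-central distributions puts the loss at about 25–40%.

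**Off-centre cuts.** The loss reaches about 57% for a young sample with 11% aged 36 or over, and about 63% if only 6% score 26 or more.

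**Effect on the interval.** For the same contrast between group means, the SE under the uniform age case is 0.200 × 15.5 = 3.10 against 3.58. The 95% half-width is then 6.1 instead of 7.0 points.

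**Check by simulation.** Age only, 8,000 regression runs with a t test: 14.6% against 20.5% at D = 5, and 61.3% against 76.1% at D = 10. These are slightly lower than the formula, with the same gain.

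**The opposite shape.** If modification were a step exactly at the cut, the linear term would be the one to lose. In the uniform age case at D = 10, its ratio is 2.793 × √0.75 = 2.419, and power falls from 66% to about 51%.

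**The case against.** The strongest reply is that nothing here is wrong in itself. The cuts are fixed in advance, the tests are proper interaction tests, the alpha is right, and two-level subgroups are a conventional reporting format. The plan calls the results hypothesis-generating and prefers intervals to p-values, and the primary non-inferiority comparison is untouched. All of this stands, and it limits the weight of the point. It does not remove it, because the stated choice also widens the intervals the plan prefers.

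Several stronger readings are tempting but not supported:
- *That a fixed share of information is lost.* The document gives no distribution for age or baseline score and says nothing on the shape of modification. The loss is conditional.
- *That 5 points is the plan's own benchmark for an interaction.* In the sample size section it is a difference between arms. A difference between subgroups in the arm effect is another quantity, so 3, 5 and 10 points are all illustrations here. At 3 points, the size of the non-inferiority margin, the gain is small.
- *That a gradient would show for whom online delivery is inadequate.* Adequacy is judged against the margin in the whole trial. These analyses have no confirmatory role.
- *That the cut-points are at fault because no source is given.* A condensed article may leave that rationale to a fuller document.
- *That the change is free.* It brings a linearity assumption, and would cost power under a step at the cut.

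**Conclusion.** The point holds in conditional form. The protocol article tests age and baseline HAM-D-17 as modifiers only through two-level factors. Given roughly linear modification and near-central cuts, this loses about 25–40% of the information, and more with an off-centre cut. At SD 8, 80 clients and alpha 0.0167, continuous terms would raise power from about 14–16% to 21–25% for an assumed 5-point interaction and from about 60–66% to 79–86% for 10 points. For 3 points the gain is only 2–3 percentage points. Power for interactions of 5 points or less stays poor either way, so the description of these analyses as hypothesis-generating remains right. The primary result is not affected. This is a minor, optional improvement.

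**What to change.** In Additional analyses {20b}, state that the arm-by-age and arm-by-baseline-HAM-D-17 interactions will be tested with both modifiers as continuous, centred terms in the mixed-effects model already planned, and that each interaction slope will be reported with its 95% CI. Keep the 20–35/36–50 and 20–25/26-or-more groups only to display the estimated arm difference. Trauma history stays binary, and the adjusted alpha of 0.0167 is unchanged.

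The cost is one sentence of wording, with no new data, visits or clients. The downside is the linearity assumption; the displayed subgroup estimates give a rough check on it.

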### Methods for addressing non-adherence and missing data {20c}

To account for protocol deviations, primary analyses will employ both intention-to-treat and per-protocol approaches, with the intention-to-treat population including all randomized participants regardless of adherence and the per-protocol population restricted to those completing ≥ 80% of sessions with verified fidelity. For missing data, a tiered strategy will be implemented:Continuous monitoring with initiated outreach after any missed assessment to minimize attrition.Multiple imputation by chained equations using 50 imputed datasets incorporating baseline characteristics, treatment arm, and observed outcome trajectories as predictors.Sensitivity analyses comparing results with pattern-mixture models that assume different missingness mechanisms (missing at random vs. not at random).

For participants who discontinue therapy but complete all outcome assessments, their available data will be included in the mixed-effects models used for longitudinal analyses.

### Plans to give access to the full protocol, participant-level data and statistical code {31c}

The full study protocol and its findings, in the form of a de-identified aggregate participant-level dataset, will be made publicly available six months after trial completion. However, these data will only be accessible as supplementary files accompanying published research articles and book chapters that present the findings of the study.

## Oversight and monitoring

The Trial Steering Committee will comprise both trial investigators and independent members, in accordance with Medical Research Council (MRC) guidance for independent trial oversight. The committee will be chaired by an independent senior academic with expertise in clinical trials and psychotherapy research, who is not otherwise involved in the conduct of the study. In addition to the independent chair, the Trial Steering Committee will include at least two further independent members, such as an external EMDR expert and an independent biostatistician, neither of whom will be involved in participant recruitment, intervention delivery, or data analysis. These independent members will provide objective oversight of trial progress, protocol adherence, safety monitoring, and ethical conduct. Trial-involved members of the Trial Steering Committee will include the principal investigator and a co-investigator, who will provide scientific input and operational updates. Supporting members, including research assistants, psychotherapists, a data analyst, and a consulting psychiatrist, will contribute to implementation and safety reporting but will not participate in independent decision-making. The Trial Steering Committee will operate under a formal written charter defining roles, responsibilities, meeting frequency, and decision-making processes, which will be finalized prior to trial initiation. This governance structure ensures appropriate independence, accountability, and robust oversight throughout the study.

### Composition of the data monitoring committee, its role, and reporting structure {21a}

The Independent data monitoring committee will consist of the principal investigator, a statistician, an EMDR therapy expert unaffiliated with this trial, and a patient representative with lived experience of depression. The committee will function under a formal charter that clearly defines its mandate. Its responsibilities include:Conducting quarterly blinded reviews of adverse event reports and unblinded interim efficacy analyses in accordance with O’Brien–Fleming boundaries.Evaluating protocol deviations that may affect data integrity.Issuing recommendations regarding trial continuation, modification, or termination based on safety and efficacy considerations.

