### Concealment mechanism {16b}

An independent research assistant will generate the randomization sequence using covariate-adaptive algorithms accounting for age, gender, depression severity, and comorbidity, with a 1:1 allocation to treatment groups. The randomization sequence will be securely stored in password-protected documents accessible exclusively to the principal investigator and the designated research assistant, with access logs maintained for auditing purposes. Allocation concealment will be ensured until assignment, and outcome assessors and data analysts will remain blind to group allocation throughout the trial. Due to the nature of the intervention, blinding of clients to treatment delivery mode (online vs. in-person EMDR) is not feasible. Group assignment will be implemented electronically via either OpenClinica (https://www.openclinica.com) or Sealed Envelope (https://www.sealedenvelope.com) platforms, which reveal only the immediate next assignment following completion of baseline assessments. This dual protection system—combining restricted access to master randomization lists with electronic allocation masking—ensures compliance with CONSORT and SPIRIT standards for allocation concealment.

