### Implementation {16c}

Following eligibility confirmation and baseline assessments (T_1_), randomization will be executed through the designated electronic platform (OpenClinica/Sealed Envelope) by a research assistant who will not be involved in outcome measurement. The online system will be connected to the therapists’ and patients’ emails. It will automatically notify the treating therapist of the allocated intervention mode (online or in-person) and inform the patient via secure messaging, while maintaining the blinding of outcome assessors. To ensure protocol fidelity, therapists will receive arm-specific procedure checklists corresponding to their notification. The principal investigator will conduct weekly cross-checks between the electronic allocation records and physical randomization documents to detect and rectify any discrepancies.

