### Plans to promote participant retention and complete follow-up {18b}

To maximize participant retention and follow-up completion, a multipronged strategy will be employed, including:Regular check-in calls to address logistical or technical barriers.Flexible scheduling options, including evening and weekend sessions to accommodate working participants.A three-tiered follow-up procedure for missed appointments:Day 1: Email reminder.Day 3: Follow-up mobile/telephone call by a research assistant.Dedicated “therapy booster” sessions for patients showing signs of disengagement (defined as ≥ 2 missed appointments).Monthly retention reports, reviewed by the principal investigator to identify trends and adjust engagement strategies as necessary.

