### Data management {19}

All study data will be managed using a tiered framework. Each recruited participant will be assigned a unique identification number. Physical data collected on paper will be securely stored in the principal investigator’s university archive, which is restricted and access-controlled. All study data will be archived for three years following the completion or premature termination of the trial. De-identified datasets will be retained for three years post-trial to allow for potential secondary analyses or regulatory audits. Only designated research assistants will be authorized to record and analyze data, and no other individual will be permitted to access or handle it. Role-based access permissions will be implemented, with the principal investigator having full access and research assistants granted access only to specific forms relevant to their responsibilities. All databases, including online, e.g., Google Drive, or in-system, e.g., Microsoft Excel and SPSS files, will be secured using two-factor authentication. Furthermore, Data use agreements will be mandatory for all third parties requesting access to the data, ensuring strict adherence to confidentiality and ethical standards.

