### Interim analyses {21b}

The study will incorporate two strategically timed interim analyses to monitor trial progress and participant welfare. The first analysis, focused on safety monitoring, will be conducted after the initial cohort of 40 participants completes their mid-treatment assessments. This evaluation will systematically compare adverse event profiles between the online and in-person EMDR groups, with particular attention to clinically significant indicators such as dissociation rates. Should the analysis reveal substantially higher adverse events in either treatment arm—for instance, elevated dissociation occurrences in the online EMDR group—the protocol will be adaptively modified to incorporate additional stabilization sessions for affected participants while maintaining trial continuity.

The second interim analysis, designed to assess efficacy and futility thresholds, will occur when 60 participants (75% of the target sample) have completed their end-of-treatment evaluations. This analysis will employ O’Brien–Fleming statistical boundaries to determine whether the accumulating data demonstrates either compelling evidence of treatment success or insufficient likelihood of achieving meaningful results. For example, if the analysis reveals that online EMDR demonstrates near-equivalent efficacy to in-person delivery—as might be evidenced by merely a 0.5-point difference on the HAM-D-17 scale (*p* = 0.005)—the trial could be responsibly terminated early based on established efficacy. Conversely, should the data suggest minimal probability of ultimately proving non-inferiority, the futility provisions would be activated to conserve resources. These pre-specified analytical checkpoints are integrated into the study design to balance scientific rigor with ethical responsibility and operational efficiency.

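### The data monitoring committee is called independent but seats the principal investigator, who would see unblinded interim efficacy results while still running the trial

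*Protocol article*

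**What the plan says.** All references are to the protocol article.

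- **Composition of the data monitoring committee {21a}:** "The Independent data monitoring committee will consist of the principal investigator, a statistician, an EMDR therapy expert unaffiliated with this trial", plus a patient representative. Only the EMDR expert is described as unaffiliated. The duties of the committee as a whole include "unblinded interim efficacy analyses in accordance with" O'Brien–Fleming boundaries, and "Issuing recommendations regarding trial continuation, modification, or termination based on safety and efficacy considerations". No closed session, recusal or non-voting status is stated for any member. A charter is mentioned but not shown.
- **Oversight and monitoring:** the principal investigator sits on the Trial Steering Committee as a trial-involved member, separate from its independent chair and at least two further independent members.
- **Concealment mechanism {16b}:** the randomization sequence is "accessible exclusively to the principal investigator and the designated research assistant".
- **Implementation {16c}:** "The principal investigator will conduct weekly cross-checks between the electronic allocation records and physical randomization documents".
- **Procedure for unblinding {17b}:** unblinding requests go to the principal investigator, who verifies the need and discloses the allocation.
- **Plans to promote participant retention {18b}:** monthly retention reports are "reviewed by the principal investigator to identify trends and adjust engagement strategies as necessary".
- **Data management {19}:** role-based permissions apply, "with the principal investigator having full access".
- **Interim analyses {21b}:** a first, safety look takes place after 40 participants reach mid-treatment. A second look, for efficacy and futility, takes place when 60 participants have completed end of treatment.

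**The concern.** A monitoring committee that sees comparative results is kept separate from the people running the trial so that knowledge of the interim difference cannot affect the rest of the trial. Here the separation is removed by a positive statement of membership, not by an omission.

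The principal investigator has at least one expressly assigned lever on the remaining data, the engagement strategy for clients at risk of dropping out. Clients and therapists know the delivery mode. Retention bears on both the intention-to-treat and the per-protocol analyses that the protocol plans. A trial lead who knows which arm is ahead could, without intending to, direct that effort differently.

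The same person would also take part in the stopping recommendation. Interim analyses {21b} describes futility only as a minimal probability of proving non-inferiority, with no threshold. The committee therefore has to use judgement, and its independence matters for that reason.

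**Working it through.** No power or alpha figure is at issue. The check sets the sections side by side and then measures what is still open at the second look.

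**1. Label against membership.** Section {21a} calls the committee independent and names the principal investigator as its first member. Oversight and monitoring places the same person among those involved in the trial. The two descriptions cannot both be right.

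**2. Access to results.** Section {21a} gives the unblinded efficacy analyses to the committee and excludes no member, so as written the principal investigator sees the arm difference.

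**3. Operational role.** {16c} gives the weekly allocation cross-check, {17b} the unblinding decisions and {18b} the retention strategy. All three fall to the principal investigator.

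**4. A second route to the same information.** {16b} gives the principal investigator the allocation sequence and {19} gives full data access. Together these would allow outcomes to be compared by arm at any time, without the committee. Removing the principal investigator from the committee alone would leave this route open.

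**5. What is outstanding at the second look.** Inputs are the 60 completers in {21b} and the 80 planned for the primary analysis in Clients selection and sample size {14}.
- Share observed: 60 / 80 = 75%, which reproduces the protocol's figure.
- End-of-treatment assessments outstanding: 80 − 60 = 20, and 20 / 80 = 25%.
- The 2-month follow-ups of those 20, and of the most recent completers among the 60, would also still be due.

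**6. How many clients would still be unallocated.** Inputs are 15% dropout {14}, 8–10 enrolled per month {15}, 10–14 weekly sessions {11a} and a recruitment target of 94 {14}.
- Clients enrolled to yield 60 completers: 60 / 0.85 = 70.6, about 71.
- Enrolled while the last of these finish treatment: 10 weeks × 12/52 = 2.3 months at 8 per month, about 18; 14 weeks × 12/52 = 3.2 months at 10 per month, about 32.
- Allocated at the look: 71 + 18 = 89, up to 71 + 32 = 103, which is capped at 94.

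About 89 to 94 of 94 clients would therefore already be allocated. Any influence would act mainly through the remaining sessions, retention and follow-up of those clients, and little through new allocations.

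**The case against.** Several points on the other side are fair.

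- **The charter may confine the principal investigator to open sessions.** It is not shown, so this is possible. But the membership sentence reads as full membership, and a charter that excluded the principal investigator from unblinded results would contradict it. The wording needs correcting in either case.
- **There are real safeguards.** The raters of the primary outcome and the data analysts are blinded. The data monitoring committee only recommends, and the Trial Steering Committee has an independent chair and further independent members. This stands, and it limits the likely harm. A reader might treat the trial as wholly open-label; the documents do not support that.
- **No stated blind is broken.** The principal investigator is not listed among the blinded personnel. A reader might infer that access to past allocations, for all 80 to 94 clients, is itself a breach. It is not. It matters only in combination with outcome data and interim results.
- **The 25% is not a bias estimate.** It counts the endpoints outstanding at the look.
- **The safety reviews need not contradict each other.** A reader might infer that blinded adverse-event reviews in {21a} are incompatible with the plan in {21b} to "systematically compare adverse event profiles between the online and in-person EMDR groups". The former are quarterly and the latter is a single look. The protocol's own blinding model gives analysts group codes {17a}, which would permit a comparison of coded arms. What remains is a lack of clarity: {21b} does not say who makes the comparison, and {21a} does not assign it to the committee.

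None of this answers the central point about membership and access.

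**Conclusion.** The point holds. The protocol places a person it elsewhere treats as involved in the trial on a committee it calls independent, and gives that committee unblinded efficacy results and a say in stopping. At the second look, 20 of 80 planned end-of-treatment assessments, plus later follow-ups, would be collected while the trial lead knows the interim arm difference.

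The size and direction of any resulting bias cannot be calculated from the documents, and none is claimed. Only the retention lever is expressly given to the principal investigator; influence through scheduling or fidelity feedback would be conjecture.

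The conclusion assumes that the membership sentence means what it says and that the efficacy look takes place as planned. The adverse-event wording is a minor clarification and carries no weight in this conclusion.

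**What to change.** 1. In {21a}, remove the principal investigator from committee membership and allow attendance at open sessions for progress reports only. The statistician, the unaffiliated EMDR expert and the patient representative remain.
2. State that the committee's statistician is not the trial's analyst.
3. State that interim comparative results are withheld from the principal investigator and the trial team. Limit the full data access in {19} accordingly, so that outcome data cannot be compared by arm before database lock.
4. Keep the weekly allocation cross-check in {16c} with someone other than the assistant who executes randomization. Handing it to that assistant would remove the only second-person check.
5. As a clarification, state that the committee makes the between-arm adverse-event comparison of {21b}, and reconcile this with the blinded reviews in {21a}.

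The cost is mainly protocol and charter wording and a change to data permissions. If the statistician now named is the trial's analyst, another person is needed. The change may also need ethics approval and a registry update under the protocol's amendment procedure {25}.

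Recruitment began in April 2025, so the change should be made before the 60-completer look. If that look has already taken place, the report should disclose who saw the results.
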